## Abstract

**Background:**

Mental ill health is the most frequent cause of long-term sickness absence and disability retirement in Denmark. Some instances of mental ill health might be due to long working hours. A recent large cross-sectional study of a general working population in Norway found that not only “very much overtime”, but also “moderate overtime” (41-48 work hours/week) was significantly associated with increased levels of both anxiety and depression. These findings have not been sufficiently confirmed in longitudinal studies.

**Objective:**

The objective of the study is to give a detailed plan for a research project aimed at investigating the possibility of a prospective association between weekly working hours and use of psychotropic medicine in the general working population of Denmark.

**Methods:**

People from the general working population of Denmark have been surveyed, at various occasions in the time period 1995-2010, and interviewed about their work environment. The present study will link interview data from these surveys to national registers covering all inhabitants of Denmark. The participants will be followed for the first occurrence of redeemed prescriptions for psychotropic medicine. Poisson regression will be used to analyze incidence rates as a function of weekly working hours (32-40; 41-48; > 48 hours/week). The analyses will be controlled for gender, age, sample, shift work, and socioeconomic status. According to our feasibility studies, the statistical power is sufficient and the exposure is stable enough to make the study worth the while.

**Results:**

The publication of the present study protocol ends the design phase of the project. In the next phase, the questionnaire data will be forwarded to Statistics Denmark where they will be linked to data on deaths, migrations, socioeconomic status, and redeemed prescriptions for psychotropic medication. We expect
the analysis to be completed by the end of 2014 and the results to be published mid 2015.

**Conclusions:**

The proposed project will be free from hindsight bias, since all hypotheses and statistical models are completely defined, peer-reviewed, and published before we link the exposure data to the outcome data. The results of the project will indicate to what extent and in what direction the national burden of mental ill health in Denmark has been influenced by long working hours.

## Introduction

### Mental Health and Long Working Hours

Mental health problems have become the biggest single cause for a disability benefit claim in the Organization for Economic Cooperation and Development countries. In Denmark, they account for almost 50% of all new claims [1]. The research literature suggests that some instances of mental ill health might be due to long working hours. It has been shown that long working hours are associated with short sleep [2-4] and fatigue [2,4-6], and that both of these conditions are predictors of psychiatric disorders [7-13]. There are, however, also some prophylactic effects of long working hours. All else being equal, long working hours would increase income, and thereby, decrease the risk of financial strain, which is a condition proven to be highly predictable of psychiatric disorders [14-16]. Some individuals who work long hours appear to be in a situation where there is an imbalance between the prophylactic and the pathogenic effects of the prolonged work [17]. From this viewpoint, some cases of mental ill health would be caused by long working hours, while others would be prevented in that prolonged work might solve problems which otherwise would lead to mental ill health.

### The Danish Government and Increased Working Hours

The Danish government wants to increase the total number of work hours in the nation by: (1) decreasing the number of hours that are lost due to sickness absence and early retirement, and (2) encouraging the ones that are working, to work longer hours [18]. From this perspective, we want to know if there is a positive, negative, or no correlation between long working hours and incidence of psychiatric disorders in the Danish working population, in other words, if pathogenic effects of long working hours outweighs the salutogenic effects or vice versa. We are especially interested in the situation among the people who perform moderate overtime work (41-48 work hours/week), that is, overtime work which lies within the limits of the European working time directive. If there is a nonnegligible correlation between long working hours and subsequent mental ill health, then this needs to be taken into account in the planning and evaluation of strategies aimed at getting more people to work extra hours.

The existing literature does not provide the information we need to settle this question.

### Studies and Findings

A recent large cross-sectional study of a general working population in Norway found that not only “very much overtime” (49-100 work hours/week), but also “moderate overtime” (41-48 work hours/week) was significantly associated with increased levels of both anxiety and depression [19]. These findings have, however, not been sufficiently confirmed in studies that utilize longitudinal designs. The hypothesis that “very much overtime” is a predictor of mental disorders is supported by three prospective company based studies [20-22]. Suwazono et al [20] focused on the development of mental disorders among workers in a large telecommunication enterprise in Japan. They found that the odds for having developed mental disorders at the end of a four year follow-up period were higher among those who worked > 12 hours/day at baseline than they were among those who worked ≤ 8 hours/day. The estimated odds ratio was statistically significant among the men, but not among the women. Virtanen et al [22] focused on the development of depression and anxiety symptoms in a group of middle-aged British civil servants. They found that those who worked more than 55 hours/week at baseline, compared with those who worked 35-40 hours/week, had a higher propensity for developing depression and anxiety symptoms during an approximately five year follow-up period. Based on the same database, it has also been shown that the civil servants who worked more than 55 hours/week had a higher propensity for developing sleeping disorders [21]. The latter result is, however, contradicted by a large population-based prospective study wherein the odds for having developed sleeping disorders at the end of a five year follow-up period were lower among those who often worked more than 48 hours/week at baseline than they were among other employees [23].

The company-based studies mentioned above also compared the effect of “moderate overtime” (defined as 8-12 work hours/day by Suwazono et al, and 41-55 work hours/week by Virtanen et al) [20-22] with the effect of “normal working hours” (defined as ≤ 8 work hours/day by Suwazono et al, and 35-40 work hours/week by Virtanen et al) [20-22]. The studies suggest a tendency for higher risks among those with moderate overtime work, but the contrast is not statistically significant in any of the studies.

### Aim and Hypothesis

The null-hypothesis of the present project is that long working hours, to the extent that it is currently practiced in Denmark, neither adds to nor subtracts from the national burden of mental ill health.

The project aims at testing the above hypothesis in a prospective cohort study on a random sample of the Danish working population. The null-hypothesis will be rejected if subsequent rates of mental ill health (manifested by the use of psychotropic medicine) among people with long working hours at baseline differ significantly from those among people with normal working hours. The analysis will be adjusted for gender, age, socioeconomic status, and shift work. It will only include those who are free from symptoms at baseline.

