#### Statistical Model

We will use Poisson regression to analyze incidence rates of redeemed prescriptions for psychotropic medicine as a function of weekly working hours (32-40; 41-48; > 48 hours/week). The analysis will be controlled for gender, age (10 year classes), sample (DWECS 1995; DWECS 2000; COPSOQ 2004; DWECS 2005; DANES 2008; and DWECS 2010), shift work (fixed night shifts or rotational shift work schedules vs other), and SES (legislators, senior officials and managers; professionals; technicians and associate professionals; workers in occupations that require skills at a basic level; workers in elementary occupations; and gainfully occupied people with an unknown occupation). With SES we mean socioeconomic status, according to the employment classification module, during the calendar year of the baseline interview. The logarithm of person years at risk will be used as offset. A likelihood ratio test will be used to test the null-hypothesis, which states that the analyzed rates are independent of weekly working hours. The significance level is set to 0.05.

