#### Power Calculations

Based on rates calculated through DNPR in the time period 2001-2005, we expect on average approximately 25 new cases per 1000 person years at risk (PYRS). We expect that the four follow-up periods of nonprevalent cases in the DWECS samples will provide approximately 68,000 PYRS, the five year follow-up of the COPSOQ sample will provide 12,000 PYRS, and the four year follow-up of the DANES sample will provide 16,000 PYRS. Among the ones who worked 32 or more hours per week in 2000 according to DWECS, 26.7% worked more than 40 hours/week and 10.5% worked more than 48 hours/week.

With the above data as input, Figure 1 illustrates the statistical powers to detect contrasts between normal working hours (32-40 hours/week) on one hand and “overtime work” (>40 work hours/week), “moderate overtime work” (41-48 work hours/week), and “very much overtime” (49-100 work hours/week) on the other, as a function of the true rate ratio. If, for example, the true rate ratio between moderate overtime workers and those with normal working hours is 1.2 then we have a 90% chance of detecting the difference; if it is 1.3 then the chance of detection is 99.7%. The power calculations are based on the Poisson distribution, the propagation of error formulas, and the central limit theorem.

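### The null hypothesis and promised conclusion concern the national burden, but the primary test only asks whether rates differ across three hours categories, so rejection alone does not support a burden statement

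*Protocol article*

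**What the plan says.** Three places put the question in terms of burden.

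- **The Danish Government and Increased Working Hours** (Introduction) asks "if pathogenic effects of long working hours outweighs the salutogenic effects or vice versa".
- **Aim and Hypothesis** gives the null as long hours, at the extent practised in Denmark, having no effect in either direction: they "neither adds to nor subtracts from the national burden of mental ill health". Its rejection rule treats long hours as one group, whose rates must "differ significantly from those among people with normal working hours".
- **Abstract, Conclusions** says that the results "will indicate to what extent and in what direction the national burden of mental ill health in Denmark has been influenced by long working hours".

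The operational text is in **Statistical Model** (Primary Analysis). Poisson regression models the rates "as a function of weekly working hours (32-40; 41-48; > 48 hours/week"). Then: "A likelihood ratio test will be used to test the null-hypothesis, which states that the analyzed rates are independent of weekly working hours". The test is run at the 5% level.

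No section defines a net or overall burden quantity or names a single overall contrast as confirmatory. Power Calculations does consider more than 40 hours against normal hours, but only as one of three contrasts for which power is drawn.

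**The concern.** The two nulls are not equivalent. With three categories, independence means that both overtime rate ratios equal 1, which is a single point. No net addition to the burden means only that the share-weighted sum of the two excesses is zero, which is a line through that point. Rejecting the point does not reject the line.

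The likelihood ratio test also has no direction. The category rate ratios have signs, but if they disagree, the plan has no rule for combining them into a statement about burden.

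This matters because the introduction ties the result to government policy on extra working hours. Under Secondary Analyses, the primary test also decides whether later analyses count as nested tests or as exploratory, so it should be clear which hypothesis was rejected. The protocol says that its hypotheses and models are completely specified in advance; on this point the stated hypothesis and the tested one differ.

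**Working it through.** **Inputs, all from Power Calculations**

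- Rate: "we expect on average approximately 25 new cases per 1000 person years at risk (PYRS").
- Person-years: 68,000 + 12,000 + 16,000 = 96,000, hence 96,000 × 0.025 = 2,400 expected cases.
- Exposure shares: over 48 h 10.5%; 41-48 h 26.7 − 10.5 = 16.2%; normal hours 100 − 26.7 = 73.3%.

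Sidedness is not stated. I take two-sided 0.05 for single contrasts.

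**Reproducing the stated power.** For moderate overtime against normal hours, cases = 2,400 × (0.733 + 0.162) = 2,148 and the exposed fraction is p = 0.162/0.895 = 0.181. Power = Φ(√(2,148 × p(1−p)) × ln RR − 1.96).

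- RR 1.2: Φ(3.25 − 1.96) = 90.2% (stated 90%)
- RR 1.3: Φ(4.68 − 1.96) = 99.7% (stated 99.7%)

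The inputs are therefore read as the authors used them.

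**What the test does when the net excess is zero.** Write RRm for 41-48 h and RRv for over 48 h. Zero net excess means

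0.162 (RRm − 1) + 0.105 (RRv − 1) = 0.

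Expected cases under independence are 1,759.2, 388.8 and 252.0. The noncentrality is λ = 2 Σ μ ln(μ/μ0), since both sets of expected counts sum to 2,400. The test rejects above 5.99, the 95% point of chi-square on 2 df.

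Worked case RRm = 0.90: RRv = 1 + 0.162 × 0.10/0.105 = 1.154. Expected cases are 1,759.2, 349.9 and 290.9. λ = 2 × (0 − 36.87 + 41.74) = 9.74, and the rejection probability is 80.4%.

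| RRm | RRv | λ | 2-df test rejects | Pooled >40 h vs normal rejects |
|---|---|---|---|---|
| 1.00 | 1.00 | 0 | 5% | 5% |
| 0.95 | 1.077 | 2.45 | 27% | 5% |
| 0.90 | 1.154 | 9.74 | 80% | 5% |
| 0.85 | 1.231 | 21.78 | 99% | 5% |
| 1.05 | 0.923 | 2.50 | 27% | 5% |
| 1.10 | 0.846 | 10.10 | 82% | 5% |

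Simulation with 200,000 Poisson data sets gave 80.3% at 0.90/1.154 and 99.1% at 0.85/1.231, with the pooled contrast at about 5% in both.

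**Can a net figure be estimated usefully?** In case-share form, the attributable fraction is Σ (share of cases in the category) × (RR − 1)/RR. In the worked case the case shares are 349.92/2,400 = 0.1458 and 290.88/2,400 = 0.1212. The terms are 0.1458 × (−0.10/0.90) = −0.0162 and 0.1212 × (0.1543/1.1543) = +0.0162, which sum to zero as they should. Its simulated standard error is 0.0123, so a 95% CI would be about ±1.96 × 1.23 = ±2.4 percentage points.

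All of this is unadjusted, without covariates or overdispersion.

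**The case against.** The strongest reply is that the authors say elsewhere what they mean. The Research Project (Discussion) ties the societal perspective to the rates within and beyond the EU directive limit, each compared with normal hours. Those are two category-specific comparisons, and a 2-df test suits them. The introduction also singles out the 41-48 hour group, which a net figure would hide. Statistical Model states its own null openly, and the fitted model gives a signed rate ratio for each category. All of this stands. It is why the test and the categories should stay.

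It does not remove the mismatch. Aim and Hypothesis and the abstract still announce a verdict on burden, and two category rate ratios give one only when they agree or when a rule combines them.

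A reader might infer from the table that the plan has an 80-99% chance of a false conclusion. The documents do not support that. Those figures need effects of about 10-15% one way in one group and about 15-23% the other way in the other, in exactly the cancelling ratio. Along the zero-net line the probability runs from 5% to nearly 100%. Under Studies and Findings, the cross-sectional study found both overtime categories raised and the company-based studies tend the same way; one population-based study found lower odds of sleeping disorders above 48 hours. The mixed effects described in the introduction are opposing mechanisms, not opposite signs by hours category. And where a crossover exists, rejection is correct under the null of Statistical Model. It is an error only if read as rejecting the burden null.

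**Conclusion.** The concern holds as a mismatch between the stated hypothesis, the tested hypothesis and the promised conclusion. It does not show an invalid test. A significant likelihood ratio test would show that redemption rates differ across hours categories. It would not by itself show that long hours add to or subtract from the burden, or by how much.

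The size depends on the true pattern: about 27% rejection at zero net excess for RR 0.95/1.08 and 80% for 0.90/1.15, against 5% for the pooled contrast. These are illustrations on the protocol's planning figures, without adjustment, for a crossover that the cited literature does not particularly suggest. The mismatch in wording does not depend on them. It is worth correcting because the primary conclusion is meant to inform policy and the repair is small.

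**What to change.** 1. Keep the likelihood ratio test and report both category rate ratios with confidence intervals.
2. Restate the null in Aim and Hypothesis as: redemption rates do not depend on hours category. Align the rejection rule there with the three categories.
3. Prespecify one net summary from the same adjusted model, with a 95% CI: either the adjusted attributable fraction in case-share form (sum over 41-48 and over 48 h of the proportion of cases in the category times (RR − 1)/RR) or a model-standardised equivalent. Do not use the version based on exposure shares, Σp(RR − 1)/[1 + Σp(RR − 1)]. It is biased under confounding when adjusted rate ratios are put into it, and this model adjusts for gender, age, sample, shift work and SES.
4. Base any statement that long hours add to or subtract from the burden on that estimate, its sign and its interval. Word it as an association with treated cases among workers with 32 or more weekly hours, in keeping with the protocol's own caution about etiological claims. Amend the abstract's conclusion to match.

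The cost is one derived quantity from a model already planned, plus rewording. No new data are needed and the primary test is unchanged. The downside is that a significant omnibus test may come with a net interval that includes zero, and the report must then say both.

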## Methods

### Ethics Approval

The study will comply with The Act on Processing of Personal Data (Act No. 429 of May 31, 2000), which implements the European Union Directive 95/46/EC on the protection of individuals.

### Data Material

The data material of the project will be obtained through a linkage of data from the Copenhagen Psychosocial Questionnaire (COPSOQ) study sample of 2004, the Danish National Working Environment Survey (DANES) of 2008, and the Danish Work Environment Cohort Study (DWECS) of 1995, 2000, 2005, and 2010 with data from the Central Person Register (CPR), the Employment Classification Module (ECM), and the Danish National Prescription Registry (DNPR). The participants’ unique personal identification numbers will be used as the key in the linkage procedure. DNPR covers all purchases of prescription drugs at pharmacies in Denmark since 1995 [24]. The CPR has existed since 1968, and contains dates of deaths and migrations in the Danish population [25]. A person’s occupation, industry, and socioeconomic status are, as of 1975, registered annually in the ECM [26]. Socioeconomic status is coded in accordance with Statistics Denmark’s official socioeconomic classification [27]. The socioeconomic status (SES) code among employees is based on the first digit of the Danish version of the International Standard Classification of Occupations (DISCO-88) [28], and contains the following categories: (1) legislators, senior officials, and managers (DISCO-88 group 1), (2) professionals (DISCO-88 group 2), (3) technicians and associate professionals (DISCO-88group 3), (4) workers in occupations that require skills at a basic level (DISCO-88 group 4-8), (5) workers in elementary occupations (DISCO-88 group 9), and (6) gainfully occupied people with an unknown occupation (missing DISCO-88 code).

The COPSOQ study sample is a random sample, which comprises 4732 people, 20-59 years of age, whereof 3517 are wage earners [29]. DANES is based on a random sample of the Danish population in 2008. It contains responses from 6531 people 18-59 years of age, of which 4919 are employees. The DWECS is an open cohort study, which was initiated in 1990 with a random sample of people 18-59 year of age in the Danish population. The cohort has thereafter been supplemented with young people and immigrants so as to obtain a representative cross-sectional study of at least 5000 employees every fifth year [30].

The reported response rates were 80, 75, 60, 62, 66, and 48 percent for DWECS 1995 [31]; DWECS 2000 [31]; COPSOQ 2004 [29]; DWECS 2005 [32]; DANES 2008 [33]; and DWECS 2010 [34], respectively. These response rates are, however, only correct for the data that were collected prior to 2000. In May 2000, a new law was passed which made it easier for citizens to be registered as permanent nonrespondents in research surveys based on random samples from the central person register; a registration which protects them from being contacted by researchers. The reported response rates above do not take the registered nonrespondents into account. For example, 14% of all employees in Denmark were registered as permanent nonrespondents in 2008 [35]. If we take people from this group into account then the response rate for the DANES survey in 2008 will fall from the reported 65.88% (6531/9913) to 56.66% (6531/11,527).

The COPSOQ, the DANES, and the DWECS surveys contain person-based information on weekly working hours, calculated by adding the hours worked in secondary jobs to the ones in a primary job. The wording of the questions differs, however, slightly between the various questionnaires. The DWECS questionnaires of 1995, 2000, and 2005 ask for weekly working hours in current jobs or (if the person is momentarily out of work) in the last held job. DWECS 2010 asks for current weekly working hours without further specification. COPSOQ and DANES ask for average working hours during the one year period preceding the time of the interview. The COPSOQ questionnaire only allowed participants to report between 0 and 99 working hours per week, while the other questionnaires allowed an unlimited number of hours. Another peculiarity of the COPSOQ questionnaire is that it uses a single question to ask for the combined number of hours worked in primary and secondary jobs, while the other questionnaires use one question for the number of hours worked in the primary job and another one for the hours worked in secondary jobs. The surveys also contain information on the participants’ normal work schedules. Again, the questions and response categories vary slightly between the questionnaires, but all of them can identify workers who are either on fixed night shifts or rotational shift work schedules. The exact wordings (in Danish) of the used questions are given in the appendix (see Multimedia Appendix 1). A translation into English is given; see Multimedia Appendix 2.

